| PROCEDURE                                  | 
Volunteers will be screened, enrolled and followed by the clinical investigator, PD [name] at the Clinical Research Centre of the Kantonsspital Basel.
 
At the screening-visit (days -7 to -5) and after written informed consent has been obtained, the eligible healthy subjects are randomized to vaccination with either three injections of PEV 301 10 µg (Group A) or PEV 302 10 µg (Group B) or PEV 301 50 µg (Group C) or PEV 302 50 µg (Group D) or PEV 301 50 µg plus PEV 302 50 µg (Group E) or virosomes alone (group F) at days 1(+2), 64(+2) and 183(+2).
 
If possible 23 men and 23 women should be enrolled; however, if it is not possible to have an equal sex distribution, the groups can be filled with participants of either sex.
 
The 18 volunteers recruited in October will first be stratified into males and females and then randomized in blocks of 9 (1 block = females, 1 block = males) into 3 groups: Group A (n= 8) will be vaccinated with 10 µg PEV 301, Group B (n = 8) will be vaccinated with 10µg PEV 302, and 2 volunteers will receive virosomes alone (Group F) 5 weeks later again 18 volunteers have to be recruited, they first will be stratified into males and females and then randomized into 3 groups: group C (n = 8) will be vaccinated with 50 µg PEV 301, group D (n = 8) with 50 µg PEV 302, and 2 volunteers will receive virosomes alone (Group F).
 
5 weeks after the 2nd vaccination of groups C and D 10 volunteers will be randomized in blocks of 5 to either group E (n = 8) receiving the combination of 50 µg PEV 301 plus 50 µg PEV 302 or group F (n = 2) receiving virosomes alone.
 
Immunogenicity assessments for humoral immune response are made at baseline (screening blood sample on days -7 to -5), on the days of the 2nd and 3rd vaccination (pre-vaccination samples) as well as 21 (+5) days after each vaccination.
 
Cell mediated immune response will be assessed in groups C, D, E and F only, at baseline (during screening), and 21 (+5) days after each vaccination.
 
Safety assessments are made by the investigator at baseline (before the 1st immunization) and before the 2nd and 3rd immunization as well as 2 (+1) and 7 (+2) days after each immunization.
 
After each immunization the volunteers have to remain in the clinic for a 30 minutes period for the assessment of local and systemic reactions.
 
The volunteers themselves have to fill an adverse event report form (diary card) for a 4 day observation period after each vaccination. Health status will be checked before each immunization, and on days 21 (+5) 85 (+2) and 204 (+2).
 
Standard blood chemistry and hematology will be assessed at the screening visit (days -7 to -5), prior to each vaccination as well as 7 (+2) and 21 (+5) days after each vaccination.
 |                     |                                                                                                                                                          |                 |                                          |

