## 3 Study Design

This prospective phase I, single centre, randomized, single blind, placebo controlled, dose escalating study will be conducted in 46 healthy adult volunteers. Eligible study participants will be randomized into six groups: PEV 301 10 µg (group A, n = 8) or PEV 302 10 µg (group B, n = 8) or PEV 301 50 µg (group C, n = 8) or PEV 302 50 µg (group D n = 8) or PEV 301 50 µg plus PEV 302 50 µg (group E, n = 8) or virosomes alone (group F, n = 6).

Study participants will be vaccinated three times, i.e. at days 1, 64(+2) and 183(+2) and followed-up 3 times after each vaccination. If any of the study groups does not show any immune response 3 weeks after the 2nd vaccination, no 3rd vaccination will be given to that group, i.e. the study for that group will be terminated 3 weeks after the 2nd vaccination.

Groups C & D (PEV 301 50 µg; PEV 302 50 µg) will be started 5 weeks after the 1st vaccination of groups A, B.

Group E (PEV 301 plus PEV 302) will be started 5 weeks after the 2nd vaccination of groups C and D.

Group F will be distributed and serve as a control in all groups receiving the active product.

The total duration of the study for each participant is 31 weeks, the number of visits is 13.

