## 6.3 Treatment allocation and randomization

Randomization will be computer generated. The investigator will receive envelopes with numbers (1 to 46) corresponding to the sequence of assignment to the study. In the envelope the assignment to the study group will be determined.

The 18 volunteers recruited in October will first be stratified into males and females and then randomized in blocks of 9 (1 block = females, 1 block = males) into 3 groups: Group A (n = 8) will be vaccinated with 10 µg PEV 301, Group B (n = 8) will be vaccinated with 10µg PEV 302, and 2 volunteers will receive virosomes alone (Group F). If it is not possible to have an equal sex distribution, the blocks can be filled with participants of either sex.

5 weeks later again 18 volunteers have to be recruited, they first will be stratified into males and females and then randomized into 3 groups: group C (n = 8) will be vaccinated with 50 µg PEV 301, group D (n = 8) with 50 µg PEV 302, and 2 volunteers will receive virosomes alone (Group F).

5 weeks after the 2nd vaccination of groups C and D 10 volunteers will be randomized in blocks of 5 to either group E (n = 8) receiving the combination of 50 µg PEV 301 plus 50 µg PEV 302 or group F (n = 2) receiving virosomes alone.

| Time          | N  | Dose       | PEV 301 | PEV 302 | PEV 301+302 | virosomes |
|---------------|----|------------|---------|---------|-------------|-----------|
| November 2003 | 18 | 10 µg      | 8       | 8       |             | 2         |
| December 2003 | 18 | 50 µg      | 8       | 8       |             | 2         |
| March 2004    | 10 | 50 + 50 µg |         |         | 8           | 2         |

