#### General adverse events

This is the first study in men with PEV 301 and PEV 302, therefore, general solicited adverse events related to PEV 301 and PEV 302 will be determined in this study.

As a consistent method of soliciting adverse events, the subject should be asked a non-leading question such as:

"Have you felt different since receiving the vaccine or since the previous visit?"

Adverse events already documented in the CRF, i.e. at a previous assessment, and designated as 'ongoing' should be reviewed at subsequent visits, as necessary. If these have resolved, the documentation in the CRF should be completed. If an adverse event changes significantly in frequency or intensity during a study period, a new record of the event will be started.

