### 9.4 Data and Safety Monitoring Board

A Data and Safety Monitoring Board (DSMB) will be established if one of the following situations occurs:

- One or more subjects experienced a serious adverse reaction assessed as related to the vaccine by the investigator
- One or more subjects experienced anaphylaxis
- Two or more subjects in a single dose and antigen cohort experienced a severe adverse event not explained by a diagnosis unrelated to vaccination. (For grading of severity see Appendix 4)

The DSMB will then analyze the data and decide on the continuation of the study.

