## **10.8 Interim analysis**

An interim analysis will be performed after obtaining the results following the second injection of vaccine. Data will be collected in study week 13 (visit 9). If no immune response or a response considered being sufficient are seen in one of the study groups after 2 vaccinations, the study for this group will be terminated, i.e. no 3rd vaccination will be given.

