## 12.9 Early termination

It is Pevion's intention that this study is carried out to its conclusion, but PD [name] must be aware that for a number of reasons, the study may need to be stopped prior to their conclusion. Pevion Biotech Ltd., therefore, reserves the right to terminate this Agreement:

- a. immediately upon a substantial breach of the terms either of the Agreement or of the conduct of the protocol;

- b. in the event of irregularities in the method by which the study is carried out and although capable of being rectified, are not rectified within thirty (30) days of notice from Pevion Biotech Ltd. / PMU/STI requiring this.
- c. immediately, if this is necessary in the interests of health and safety of the study subjects, or as a result of an order of any government authority or court of law.

In the event of early termination, PD [name] will cease use of the investigational drug immediately. All CRFs outstanding must be completed and returned to Pevion Biotech Ltd. together with completed drug inventory, records and remaining trial material.

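### Both steps of this first-in-human dose escalation start on the calendar alone: no safety review is required before either step, and no hold on vaccination is stated while a DSMB is being formed

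*Protocol*

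**What the plan says.** Section 3 (Study Design) describes a dose-escalating phase I study in 46 volunteers with two timed steps. For the first, "Groups C & D (PEV 301 50 µg; PEV 302 50 µg) will be started 5 weeks after" the first vaccination of groups A and B. For the second, "Group E (PEV 301 plus PEV 302) will be started 5 weeks after" the second vaccination of groups C and D. Section 6.3 repeats the first step as a recruitment instruction, "5 weeks later again 18 volunteers have to be recruited", and the Procedure entry of the Synopsis has the same text. The Flow Chart turns both steps into fixed study weeks.

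Safety decisions appear in three other places:

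- **Section 9.4 (DSMB).** A board is set up only if one of three things happens: a related serious reaction in at least one subject, anaphylaxis in at least one subject, or unexplained severe events in at least two subjects of the same dose-and-antigen cohort. After that, "The DSMB will then analyze the data and decide on the continuation of the study".
- **Section 10.8 (Interim analysis).** The rule begins "If no immune response or a response considered being sufficient are seen in one of the study groups after 2 vaccinations" and leads only to withholding the third dose from that group.
- **Section 12.9 (Early termination).** The sponsor reserves the right to terminate "immediately, if this is necessary in the interests of health and safety of the study subjects".

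**The concern.** In a dose-escalating first-in-human trial with safety as the primary objective, what was seen at the lower step should decide whether the next one opens. Here the only stated condition is that five weeks have passed. The day 2, 7 and 21 visits and the laboratory tests supply the data, but no section says that someone must look at them for the cohort as a whole and record a decision before 50 µg, or both antigens together, is first given.

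There is a second gap after a trigger event. The DSMB does not exist until then and has to be assembled. Section 9.4 does not say what happens in the meantime to vaccinations or cohort starts already on the calendar. If a trigger occurred in study week 4 or 5, groups C and D would still be scheduled for their first dose in week 6.

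At stake is avoidable exposure of healthy volunteers. Section 1.5 names anaphylaxis and immune-mediated organ damage among the potential risks.

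**Working it through.** **1. The protocol's own timing.** From the Flow Chart:

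| Step | Reference dose | 21-day safety labs | Next cohort screened | Next cohort's first dose | Interim analysis of the earlier cohort |
|---|---|---|---|---|---|
| A/B to C/D | week 1 (dose 1) | week 4 | week 5 | week 6 | week 16 |
| C/D to E | week 15 (dose 2) | week 18 | week 19 | week 20 | week 22 |

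The five-week intervals reproduce: 6 − 1 = 5 and 20 − 15 = 5.

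**2. Can the interim analysis serve as the gate?** No. It falls 16 − 6 = 10 weeks after the first 50 µg dose and 22 − 20 = 2 weeks after the first combination dose. Its criterion is immune response, not safety.

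**3. Are the safety data available in time?** Yes. Five weeks is 35 days.

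- The third follow-up visit is 21 (+5) days after vaccination, so 35 − 26 = 9 to 35 − 21 = 14 days remain before the next cohort's first dose.
- Section 5.2.3 gives this visit as 22 (+5) days. On that reading 35 − 27 = 8 to 35 − 22 = 13 days remain.
- The 30-day adverse event recording period in section 8.2 ends 35 − 30 = 5 days before the next step.
- Screening is on days −7 to −5. Counted to the earliest screening day, about 9 − 7 = 2 to 14 − 7 = 7 days remain.

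**4. Who is exposed?** Volunteers after the first cohort number 18 + 10 = 28. Of these, 2 + 2 = 4 receive virosomes alone, leaving 28 − 4 = 24 (C 8, D 8, E 8). The dose step is 50/10 = 5-fold for the 16 in C and D. The 8 in E receive 50 µg of each antigen together.

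**5. Do the DSMB triggers stand in for a review?** Only in part. The severe-event trigger needs two subjects in one dose-and-antigen cohort. One unexplained severe non-serious event in group A and one in group B would not meet it, nor would moderate laboratory abnormalities in most of a cohort.

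As an illustration, assume a per-subject probability p of a qualifying severe, non-serious event. The protocol gives no such rate, so 10% to 30% is an assumed range. For a group of 8, P(at least 2) = 1 − (1 − p)^8 − 8p(1 − p)^7, and P(exactly 1) = 8p(1 − p)^7:

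| Assumed p | P(at least 2 of 8): trigger met | P(exactly 1 of 8): trigger not met |
|---|---|---|
| 10% | 0.19 | 0.38 |
| 20% | 0.50 | 0.34 |
| 30% | 0.75 | 0.20 |

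At a true rate of 20%, a group of 8 would miss this trigger about half the time, and the next step would open with no required decision.

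**6. Other safeguards.** Section 4.4 stops further doses for the affected individual, not the cohort. Sections 8.3 and 8.8 require the investigator to evaluate adverse events at each visit and to report serious ones within one calendar day. Neither is tied to opening a cohort. Section 12.9 is a discretionary sponsor right with no scheduled review.

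**The case against.** The strongest reply is that the trial is not unguarded. One investigator at one centre sees every subject about 2, 7 and 21 days after each dose and evaluates all adverse events. Serious events also go to the ethics committee. Section 11 commits the trial to GCP and the Declaration of Helsinki, whose text in Appendix 1 obliges the team to stop if continuing may harm a subject. Section 9.4 sets cohort-level triggers in advance, and one related serious reaction or one anaphylaxis is enough. It can also be read as making continuation depend on the board's decision, since nothing says that vaccination carries on meanwhile.

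These points have weight. A flagrant problem would probably be noticed, and the five-week interval may have been chosen to leave room for a look. But a general duty to stop is not a scheduled review with a recorded outcome, and individual assessments are not a judgement on the cohort. On the hold, section 9.4 is silent, which leaves scheduled doses free to proceed. That part is a gap in wording rather than an instruction to continue.

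Two further objections stand in part. A single severe event falls below any two-or-more rule, so the threshold is a design choice; the remedy adds a decision, not a new threshold. And the working time is tighter than 9 to 14 days if the decision is wanted before screening and randomization. A late review could let the screening window lapse, so that the screening assessments might need repeating.

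**Conclusion.** The concern holds. Both escalation steps are conditional on elapsed time only, and no section requires a review of the earlier cohort's safety data before either. After a trigger event no hold is stated until the DSMB has decided. Under the rule as written, 24 of the 46 volunteers would receive the five-fold dose or the combination without a required cohort-level look at the preceding step.

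This is a safety gap in a rule that the protocol itself fixes. It concerns trial conduct, so a statistical analysis plan would not be the place to settle it. The conclusion rests on the text of the protocol and the Flow Chart weeks. It does not depend on the assumed event rates, which only illustrate how the severe-event trigger behaves. It should be corrected, and the existing calendar allows it.

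**What to change.** - **Sections 3 and 6.3 and the Synopsis:** make the first vaccination of C/D, and separately that of E, conditional on a documented review of the preceding cohort's safety data through the 21-day visit: after dose 1 of A/B for the first step, and after dose 2 of C/D for the second. Keep five weeks as the minimum interval.
- **Section 9.4:** state that further vaccinations and cohort starts are held from a trigger event until the DSMB has decided.

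Who reviews, and which findings stop a step, is for the sponsor and investigator to settle. The immunogenicity interim analysis can stay where it is.

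The cost is a few sentences. If the review is on time, there are no extra visits, samples or volunteers and the Flow Chart is unchanged. If it is late or a trigger occurs, a cohort may be delayed briefly, and volunteers already screened may need repeat screening once days −7 to −5 have passed.

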## **4 Study Population**

### **4.1 Number of subjects**

A total of 46 healthy adults (if possible 23 females and 23 males) will be enrolled into the study in order to reach a minimum of 34 evaluable subjects.

Only subjects for whom the investigator believes the requirements of the protocol will be complied with (e.g. completion of the diary cards, return for follow-up visits) should be enrolled in the study.

### **4.2 Inclusion criteria**

The following criteria should be checked at the time of study entry. If any does not apply at the time of study entry, the subject must not be included in the study:

1. Volunteers of both sexes, aged between 18 and 45 years.
2. Written informed consent obtained from the volunteer.
3. Free of obvious health problems as established by medical history and/or clinical examination before entering the study.
4. Body Mass Index between 18.50 and 29.99
5. For female volunteers, a negative pregnancy test and an adequate contraception throughout the study duration.

### **4.3 Exclusion criteria**

The following criteria should be checked at the time of study entry. If any apply at the time of study entry, the subject must not be included in the study:

1. Use of any investigational or non-registered drug or vaccine within 30 days preceding the first dose of study vaccine, or planned use during the study period and safety follow-up.
2. Chronic administration (defined as more than 14 days) of immunosuppressants or other immune-modifying drugs within six months prior to the first vaccine dose. (For corticosteroids, this will mean prednisone, or equivalent,  $\geq 0.5$  mg/kg/day. Inhaled and topical steroids are allowed.)
3. Any chronic drug therapy to be continued during the study period.
4. Longterm residency in a malaria endemic area in the past
5. Visit to malaria endemic area within 12 months previous to study start
6. Intention to travel to malaria endemic area during the study period
7. History of clinical malaria
8. Any confirmed or suspected acquired immunosuppressive or immunodeficient condition, including human immunodeficiency virus (HIV) infection, or history of congenital or hereditary immunodeficiency.
9. History of allergic disease or reactions likely to be exacerbated by any component of the vaccine.
10. Acute disease at the time of enrolment. {Acute disease is defined as the presence of a moderate or severe illness with or without fever. All vaccines can be administered to

persons with a minor illness such as diarrhea, mild upper respiratory infection with or without low-grade febrile illness, i.e., temperature  $<38^{\circ}\text{C}$  ( $<100.4^{\circ}\text{F}$ )

11. Acute or chronic, clinically significant pulmonary, cardiovascular, hepatic or renal functional abnormality, as determined by physical examination or laboratory screening tests.
12. Acute or chronic diabetes
13. History of chronic alcohol consumption and/or intravenous drug abuse.
14. Pregnant or lactating female.
15. Female planning to become pregnant.

If a subject signs the consent form but withdraws his/her consent after the 1st injection, he/she will abandon the study as of the date of withdrawal. The subject will attest the withdrawal on the consent form and the reason shall be noted at the end of the CRF. Data collected until the date of withdrawal will be used for the statistical analysis of safety.

If a subject is lost to follow-up or drops out, this fact shall be noted at the end of the CRF (definitions see 9.1). Data collected for such subjects will be used for the statistical analysis until the date of lost to follow-up or dropout.

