## 8.2 Surveillance period for occurrence of adverse events

All adverse events occurring within one month (minimum 30 days) following administration of each dose of vaccine/ placebo must be recorded on the Adverse Event Form in the subject's CRF, irrespective of severity or whether or not they are considered vaccination-related.

Additionally, all serious adverse events brought to the attention of the investigator during the period starting from the day of performance of the first study procedure for each subject and ending not earlier than six months (minimum 180 days) following administration of the last dose of study vaccine for that subject must be recorded. See 8.8 for instructions for recording and reporting of serious adverse events.

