**Drop-outs:**

Any subject for whom data is available for at least one follow-up visit but did not complete the study as foreseen in the protocol.

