### 9.3 Procedures for handling subjects discontinued

Investigators should make an attempt to contact those subjects who do not return for scheduled visits or follow-up. Information gathered should be described on the Study Conclusion page of the CRF and on Medication/Adverse event forms.

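### Section 4.3 stops using a drop-out's data at the date of dropout, with no exception for safety, although Sections 8.2 and 9.3 go on recording that volunteer's adverse events

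*Protocol*

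**What the plan says.** Two rules stand together at the end of Protocol Section 4.3. The first covers withdrawal of consent after the first injection: "Data collected until the date of withdrawal will be used for the statistical analysis of safety". The second covers loss to follow-up and dropout: "Data collected for such subjects will be used for the statistical analysis until the date of lost to follow-up or dropout". The second is not confined to any type of data.

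Section 9.1 defines a drop-out as "Any subject for whom data is available for at least one follow-up visit but did not complete the study as foreseen in the protocol". It defines a subject lost to follow-up as one vaccinated on Day 1 from whom nothing further was ever obtained.

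The recording rules are longer than the analysis rule:

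- **Section 8.2, AEs:** "All adverse events occurring within one month (minimum 30 days) following administration of each dose of vaccine/ placebo must be recorded".
- **Section 8.2, SAEs:** those that come to the investigator's notice are recorded over a period "ending not earlier than six months (minimum 180 days) following administration of the last dose of study vaccine for that subject must be recorded".
- **Section 9.3:** "Investigators should make an attempt to contact those subjects who do not return for scheduled visits or follow-up". What is learned has a fixed destination: "Information gathered should be described on the Study Conclusion page of the CRF and on Medication/Adverse event forms".

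The analysis sections (10.6, 10.7.1 and 10.9) describe listings, frequency tables and the safety population. None says when a drop-out's events stop counting.

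**The concern.** The protocol asks for safety information on a volunteer after dropout and, by the wording of Section 4.3, ends the analytical use of that volunteer's data at the dropout date. An AE or SAE that is first recorded later would be in the case report form but not in the incidence tables.

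Safety and tolerability are the primary objective (Section 2.1), and Section 10.4 states as a hypothesis that no SAE attributable to either vaccine occurs. A statement of that kind is overturned by a single event, so a rule that can remove a single recorded event matters even in a small descriptive study. Active groups have 8 volunteers, and Section 5.5 says that drop-outs are not replaced.

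**Working it through.** The point concerns a data-handling rule, so the main check sets the sections side by side. The arithmetic only illustrates scale.

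**Step 1. Does the cut-off in 4.3 cover safety?** The consent-withdrawal rule just before it names the safety analysis. The dropout rule refers to the statistical analysis without qualification. On its wording it includes safety.

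**Step 2. Do the recording periods end at dropout?** No. The AE period in 8.2 runs from each dose and the SAE period from the subject's own last dose. Neither mentions dropout. Section 9.3 adds an active attempt to obtain information from people who have stopped coming.

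**Step 3. Does another section restore these events to the analysis?** Section 10.9 keeps a drop-out in the safety population after one dose and one set of follow-up data, which settles who is counted but not until when. Sections 10.6 and 10.7.1 describe outputs and set no rule for drop-outs. Nothing overrides 4.3.

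**Step 4. Which subjects are affected?** Drop-outs as defined in 9.1. For subjects lost to follow-up the same section says that no safety information ever arrived, so there is nothing to omit.

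**Step 5. A concrete case (assumed).** A volunteer attends the visit 7 days after a dose, drops out on that date, and later reports by telephone an event that began 15 days after the dose. Since 15 is less than 30, the event is recorded under 8.2, and 9.3 puts it on the AE form. Since 15 is later than 7, the rule in 4.3 leaves it out. The same event in a volunteer who stayed would be tabulated.

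**Step 6. Illustrative scale.** The protocol's own total reproduces: 5 groups × 8 + 6 = 46. It gives no dropout rate, event rate or precision target, so one omitted event is assumed. Exact (Clopper-Pearson) 95% limits with n = 8:

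- x = 0: upper limit = 1 − 0.025^(1/8) = 0.369; lower limit 0.
- x = 1: lower limit = 1 − 0.975^(1/8) = 0.003. The upper limit solves (1 − p)^8 + 8p(1 − p)^7 = 0.025, giving p = 0.527.

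| Set | Event omitted under 4.3 | Event counted |
|---|---|---|
| One active group, n = 8 | 0/8 = 0% (0 to 36.9%) | 1/8 = 12.5% (0.3 to 52.7%) |
| All active groups, 5 × 8 = 40 | 0/40 = 0% (0 to 8.8%) | 1/40 = 2.5% (0.1 to 13.2%) |

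The denominator is the same in both columns, because 10.9 keeps the drop-out in the safety population.

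**The case against.** The best reply is that the sentence in 4.3 is a rule of inclusion: partial data from non-completers are kept and not thrown away. That may well have been the intention. But the sentence also names an end date, and an analyst who follows it would stop there.

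A second reply is that the date of dropout is undefined. If it is the date on which the case is closed, information from a 9.3 contact could fall before the cut-off. This stands, and it weakens the conflict with 9.3. It does not help with an SAE that reaches the investigator later, within the 180 days of 8.2.

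A third reply is that little hangs on it. SAEs are still reported within one calendar day (8.8), and the events that trigger a safety board (9.4) do not depend on 4.3. Section 10.5 says the study is not powered for differences between regimens, and logistic regression is reserved for event types occurring 10 or more times (10.6). All of this is right: the point concerns the reported incidence, not oversight or the group tests.

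A reader might infer more than the document supports:

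- **That the cut biases AE rates most where tolerability is worst.** Section 9.2 lists adverse events as a reason for dropout, but the event that causes dropout comes before it and is counted. Only a later event or a worsening can be lost, and no rate is given for either.
- **That a volunteer who stops vaccination but keeps attending loses all later data.** Sections 4.4 and 8.10 expressly allow such subjects to continue other procedures, so they are not clearly drop-outs.
- **That most of the safety data are discarded.** After dropout at the 7-day visit, 180 − 7 = 173 days of the SAE period remain, but that is calendar time, not data. Much of that period lies beyond scheduled visits for completers too.
- **That the plan tolerates 46 − 34 = 12 drop-outs (26%).** The Synopsis gives the 34 as evaluable for immunogenicity. A volunteer can fail that standard and remain fully in the safety data.

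**Conclusion.** The contradiction holds for drop-outs. Sections 8.2 and 9.3 provide for recording events after dropout, 4.3 ends the use of those subjects' data at dropout without excepting safety, and no analysis section repairs this. Followed literally, the plan can leave a recorded AE or SAE out of the primary safety tables.

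Its size cannot be derived from the document. The 12.5-point change in a group of 8 is conditional on one event being recorded after dropout and omitted. The conclusion rests on reading the 4.3 sentence as written and on a dropout date earlier than the date of the event or its report. It does not extend to subjects lost to follow-up as defined in 9.1, to the separate consent-withdrawal rule, or to expedited reporting and the safety board triggers.

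**What to change.** In Section 4.3, replace the dropout sentence with a statement that, for drop-outs, every AE and SAE recorded within the periods of Section 8.2, including information obtained through Section 9.3, enters the safety analysis, with the dropout date reported alongside. Say in the same place how that date is fixed. Leave the consent-withdrawal sentence as it is.

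The cost is a short amendment. The data are already to be collected, so no visits or staff are added. The drawback is that follow-up after dropout is less complete than for completers. Events recorded after dropout should therefore be flagged in the tables, so that readers can see the counts with and without them.
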